### 16.1.2 The National Institutes of Health Stroke Scale (NIHSS)

The NIHSS is a standardized neurological examination score that is a valid and reliable measure of disability and recovery after acute stroke. Scores range from 0 to 42, with higher scores indicating more severe disability. The scale includes measures of level of consciousness, extra ocular movements, motor and sensory tests, coordination, language and speech evaluations. The NIHSS will be administered at baseline, Day 5-7 or discharge if earlier. The NIHSS will only be scored by those trained and certified in the use of this scale. In this trial, we will keep a video version of NIHSS score except in those who die or are unable or refuse to take a video. The

NIHSS score will be centrally assessed by two independent certified neurologists in a blinded manner via the video. Disagreements are resolved by consensus.(See appendix 2)

### **16.1.3 European Quality Five Dimensions Five Level scale**

The EQ-5D-VAS is a generic instrument for describing and valuing health. The instrument is designed for self-completion, and respondents also rate their overall health on the day of the interview on a 0-100 hash-marked, vertical visual analogue scale. Patients who died will have a score of 0. The EQ-5D-VAS will be administered on Day 90±7 by those trained in the use of this scale. (See appendix 3)

## **16.2 Assessment of safety**

### **16.2.1 Mortality at 90±7 days**

Mortality at 90±7 days is one of the most important safety endpoints of the MARVEL trial. Mortality rates are defined as the number of deaths observed divided by the number of subjects observed over the 90-day study period.

### **16.2.2 Symptomatic Intracranial Haemorrhage**

In addition to mortality, we will investigate SICH being the most feared complication for acute ischemic stroke. SICH within 48 hours will be adjudicated by an independent Imaging Core Laboratory and the Clinical Events Committee according to the Heidelberg Bleeding Classification. SICH is diagnosed based on a combination of: 1) clinical deterioration, 2) imaging findings, and 3) causal

relatedness assessment. Clinical deterioration is defined as any of the following conditions: 1) NIHSS score increased more than 4 points than that immediately before worsening; 2) NIHSS score increased more than 2 points in one category; 3) Deterioration led to intubation, hemicraniectomy, external ventricular drain placement or any other major interventions. The imaging criteria are presence of parenchymal hematoma type 2 (PH2), parenchymal hematoma type 1 (PH1), remote intracerebral haemorrhage (RIH), subarachnoid haemorrhage (SAH), intraventricular haemorrhage (IVH), or subdural haemorrhage (SDH). When clinical deterioration and PH2 co-occur, the event is automatically categorized as SICH. When clinical deterioration and PH1/RIH/SAH/IVH/SDH co-occur, the event is deemed SICH if it is judged that the haemorrhage contributed substantially to the clinical worsening. When clinical deterioration occurs only with haemorrhagic infarction type 1 or 2 (HI1 or HI2), the event is automatically classified as not SICH.

### **16.2.3 Any ICH within 48 hours**

The statistical analysis of differences in proportions of patients with any radiologic ICH within 48 hours between Methylprednisolone and Placebo groups will be performed.

The central reading will classify ICH according to the following intracerebral subtypes:

- Haemorrhagic infarct type 1 or type 2;
- Parenchymal hematoma type 1 or type 2;

- Remote intraparenchymal haemorrhage;
- In addition, intraventricular haemorrhage, subarachnoid haemorrhage, subdural haemorrhage, or epidural haemorrhage will be noted.

#### **16.2.4 Proportion of patients with pneumonia**

Pneumonia is considered when at least 2 signs (body temperature > 38°C; leukocytosis >12 000/mL, or leukopenia <4000/mL; purulent pulmonary secretions) associated with the appearance of a new infiltrate are present or when changes occur in an existing infiltrate on chest x-ray. If necessary, the diagnosis will be confirmed by a respiratory tract sample using a quantitative culture with a predefined positive threshold of  $10^4$  colony-forming units per milliliter (CFU/mL) for a bronchoalveolar lavage or non bronchoscopic sample, of  $10^3$  CFU/mL for a protected specimen brush and of  $10^6$  CFU/mL for a tracheal sample. The incidence of pneumonia will be reported by local investigators.

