## **Infections**

### ***General***

Patients who are on corticosteroids are more susceptible to infections than are healthy individuals. There may be decreased resistance and inability to localize infection when corticosteroids are used. Infections with any pathogen (viral, bacterial, fungal, protozoan, or helminthic) in any location of the body may be associated with the use of corticosteroids alone or in combination with other immunosuppressive agents. These infections may be mild, but can be severe and at times fatal. With increasing doses of corticosteroids, the rate of occurrence of infectious complications increases. Corticosteroids may also mask some signs of current infection. Do not use intraarticularly, intrabursally or for intratendinous administration for local effect in the presence of acute local infection. A study has failed to establish the efficacy of methylprednisolone sodium succinate in the treatment of sepsis syndrome and septic

shock. The study also suggests that treatment of these conditions with methylprednisolone sodium succinate may increase the risk of mortality in certain patients (i.e., patients with elevated serum creatinine levels or patients who develop secondary infections after methylprednisolone sodium succinate).

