### **7.2.5 Clinical Events Committee**

The Clinical Events Committee will be comprised of three expert physicians independent of the investigational sites. This committee will validate all the complications that occur over the course of the study and categorize each for severity and relatedness according to the definition in the AE section. The Clinical Events Committee can request any additional source information and images supporting the AEs to assist with the adjudication.

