### **15.3.2 Secondary Safety Endpoints**

- Proportion of patients with any radiologic intracranial haemorrhage within 48 hours after treatment;
- Proportion of patients with pneumonia;
- Proportion of patients with gastrointestinal haemorrhage within 7 days after EVT;
- Incidence of serious adverse events.
- Incidence of any adverse events.

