### **18.4 Safety analysis**

Safety outcomes include incidence of overall mortality at 90 ( $\pm$ 7) days after randomization, the proportion of patient with SICH within 48 hours after treatment, the proportion of patient with any ICH within 48 hours after treatment, proportion of patients with pneumonia and proportion of patients with gastrointestinal haemorrhage within 7 days after EVT;. The safety analysis will be performed on the Safety

Population. The incidences of each outcome will be compared via Chi-square test or Fisher's exact test. The modified Poisson regression models will be fitted to estimate the risk-ratio associated with the treatment effect. Risk ratio with 95% CI will be reported. Patients with missing outcome will not be included in the regression analysis. Additionally, Log-Rank test and the Kaplan-Meier estimates will be plotted over the observation period of 90 days for mortality. Cox regression model will be employed to calculate the hazard ratio with 95%CI.

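### The white-cell thresholds in the pneumonia definition are written per mL, 1000-fold below a workable scale, so the definition is wrong as written

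*Supplement*

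**What the plan says.** Section 16.2.4 (pneumonia) of protocol version 2.0 opens the rule with "Pneumonia is considered when at least 2 signs (body temperature > 38°C". It then gives the white-cell sign as "leukocytosis >12 000/mL, or leukopenia <4000/mL", and purulent pulmonary secretions as the third sign. The signs must accompany a new infiltrate. A further limb concerns changes in an existing infiltrate on chest x-ray. Quantitative culture may confirm the diagnosis where necessary, and its thresholds are given in "colony-forming units per milliliter (CFU/mL").

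The section ends: "The incidence of pneumonia will be reported by local investigators". Section 7.2.5 says of the Clinical Events Committee: "This committee will validate all the complications that occur over the course of the study".

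Section 15.3.2 lists "Proportion of patients with pneumonia" as a secondary safety endpoint. Section 18.4 compares it in the Safety Population by chi-square or Fisher's exact test and adds a regression estimate: "The modified Poisson regression models will be fitted to estimate the risk-ratio associated with the treatment effect".

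Version 1.0 prints the same thresholds in the same unit, so the amendment did not mend them. Neither version restates them elsewhere in another unit.

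**The concern.** The numbers 12 000 and 4000 work as a pair only if they are counts per microlitre. Per mL they lie far below any white count a laboratory would report. The leukocytosis sign then no longer separates patients, and the leukopenia sign can never occur.

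This is a decision threshold in the definition of a tested endpoint, not a slip in background text. A site that applies it literally uses a looser definition than a site that corrects it silently. Section 7.1 puts the number of centres at 82, so consistent handling cannot be assumed. A report that reproduced the definition from the protocol would also publish a wrong criterion for a harm of direct interest with a corticosteroid.

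**Working it through.** **Inputs.** From section 16.2.4 (pneumonia): cut-offs of 12 000/mL and 4000/mL, and a rule of two signs out of three plus a new infiltrate. The documents give no white-cell reference range, so counts of 0.5 to 30 ×10⁹/L are assumed below.

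**Conversion.** Count per mL ÷ 1000 = count per µL. Count per mL × 1000 ÷ 10⁹ = count in ×10⁹/L.

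| As written | Per µL | ×10⁹/L | Same number read per µL |
|---|---|---|---|
| 12 000/mL | 12 | 0.012 | 12 ×10⁹/L |
| 4000/mL | 4 | 0.004 | 4 ×10⁹/L |

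The ratio between the two readings is exactly 1000.

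**Literal rule against assumed counts.**

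| Count (×10⁹/L) | Per mL | Multiple of 12 000/mL | Leukocytosis as written | Leukopenia as written | Sign met if read per µL |
|---|---|---|---|---|---|
| 0.5 | 500 000 | 42 | yes | no | leukopenia |
| 4 | 4 000 000 | 333 | yes | no | neither |
| 7 | 7 000 000 | 583 | yes | no | neither |
| 12 | 12 000 000 | 1000 | yes | no | neither |
| 30 | 30 000 000 | 2500 | yes | no | leukocytosis |

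Across the whole range the leukocytosis sign is met and the leukopenia sign is not. With one sign always true, two of three becomes at least one of fever or purulent secretions.

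**Illustration of size.** Let f, s and w be the probabilities of fever, secretions and an abnormal count (read per µL), assumed independent. These values are assumptions; the documents supply none.

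- Intended rule: P = fs + fw(1 − s) + sw(1 − f)
- Literal rule: P = 1 − (1 − f)(1 − s)

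| f, s, w | Intended | Literal |
|---|---|---|
| 0.2, 0.1, 0.2 | 0.020 + 0.036 + 0.016 = 7.2% | 1 − 0.8 × 0.9 = 28% |
| 0.3, 0.2, 0.3 | 0.060 + 0.072 + 0.042 = 17.4% | 1 − 0.7 × 0.8 = 44% |
| 0.4, 0.3, 0.4 | 0.120 + 0.112 + 0.072 = 30.4% | 1 − 0.6 × 0.7 = 58% |

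These are the proportions meeting the sign component only. The infiltrate is still required, so they are not pneumonia rates.

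**Is mL meant as millilitre?** The same paragraph spells the unit out when it defines the culture thresholds, so mL there is not shorthand for something smaller. Section 9.2 gives the platelet limit in ×10⁹/L and creatinine in umol/L, so the protocol uses smaller-unit notation where it intends it.

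**The case against.** The strongest reply is that nobody would apply the clause literally. It names its signs leukocytosis and leukopenia. A reading that labels every patient with the first and none with the second contradicts those words and signals a slip. The platelet criterion in section 9.2 shows blood counts handled on the usual scale. This stands. The collapse of the two-sign rule is what the text says, not a forecast of what sites will do, and the documents give no evidence that any site would apply it literally.

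Further limits also stand:

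- The white-cell sign alone makes nobody a case, because another sign and a new infiltrate are still needed. The existing-infiltrate limb can be read as not using the count at all.
- A micro symbol lost between the source document and the published text cannot be fully excluded, although both versions print mL.
- The CRF is not shown and may already carry the right unit.
- Allocation is double-blind and randomization is stratified by centre, so different handling between centres gives no evident route to different handling between arms.

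Two stronger readings are tempting and unsupported. First, section 6.4 warns: "Corticosteroids may also mask some signs of current infection". A reader might infer that this worsens the unit error. Masking would hinder detection whatever unit is printed, and it points to fewer cases rather than a looser rule; it is a separate matter. Second, a reader might infer that section 7.2.5 already makes a blinded committee classification the analysed pneumonia endpoint. It says the members are independent of the investigational sites and validate complications. It does not call them blinded, and it does not say whose classification is analysed. Their validation may still catch some misclassified cases.

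**Conclusion.** The point holds. As printed, the thresholds are too low by a factor of 1000, and the literal rule is met by any patient who has fever or purulent secretions with a new infiltrate. The conversion is exact. That every patient meets the sign rests on the assumed range of counts, but it is insensitive to that range, since the lowest count tried is still about 42 times the cut-off.

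The practical effect is smaller than the factor suggests. Most sites would probably correct the unit silently, so what remains is possible inconsistency between centres and a stated definition that is wrong. A reader might infer that the endpoint is loosened in every patient; that would need literal application throughout, which the documents do not show. The consequence is confined to one secondary safety endpoint. The primary analysis and the sample size do not depend on it. The correction is still worth making, because the endpoint is formally tested and the remedy is cheap.

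**What to change.** Confirm the unit against the source document. If it is per mL there too, correct section 16.2.4 (pneumonia) to read above 12 ×10⁹/L (12 000 per microlitre) or below 4 ×10⁹/L (4000 per microlitre). Check that the CRF and any programmed derivation of pneumonia use the same unit. If sites have already been working from the printed text, send them a short clarification.

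The cost is one wording correction and one check of the form and the code. No new data, change of analysis or extra committee work is needed.

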#### **16.2.4 Proportion of patients with gastrointestinal bleeding.**

The statistical analysis of differences in proportions of patients with gastrointestinal bleeding within 7 days between Methylprednisolone and Placebo groups will be performed. Gastrointestinal bleeding will be reported by local investigators.

#### **16.2.5 Adverse events**

The safety assessments will include monitoring and recording adverse events, including serious and non-serious adverse events, measuring vital signs specified in

the protocol, and other protocol specified tests that are considered to be critical to the safety evaluation of the study.

Any adverse change in health or the appearance of or worsening of any undesirable sign, symptom or medical condition occurring after enrolment into the trial will be recorded as Adverse Event whether or not it is considered to be related to the study drug. An adverse event also includes any occurrence that is a new illness; aggravated in severity or frequency from the baseline condition, abnormal results of diagnostic procedures, or a combination of the above. The assessment of severity and relationship of adverse events are determined by using the following definitions.

Table 3: Severity categorization and relationship definitions of Adverse Event.

| Severity categorization |          |                                                                                                                                                                                                                                        |
|-------------------------|----------|----------------------------------------------------------------------------------------------------------------------------------------------------------------------------------------------------------------------------------------|
| Grade1                  | Mild     | It is usually transient and may require only minimal treatment or therapeutic intervention. The event doesn't generally interfere with usual activities of daily living.                                                               |
| Grade2                  | Moderate | It is usually alleviated with additional specific therapeutic intervention. The event interferes with usual activities of daily living, causing discomfort but poses no significant or permanent risk of harm to the research subject. |
| Grade3                  | Severe   | It interrupts usual activities of daily living, or significantly affects clinical status, or may require intensive therapeutic intervention.                                                                                           |

|                                |                                                                                                                                                                                                                                                                 |                                            |
|--------------------------------|-----------------------------------------------------------------------------------------------------------------------------------------------------------------------------------------------------------------------------------------------------------------|--------------------------------------------|
| Grade4                         | Life-threatening                                                                                                                                                                                                                                                | Substantial risk of dying at time of event |
| Grade5                         | Death                                                                                                                                                                                                                                                           | Death                                      |
| Relationship of adverse events |                                                                                                                                                                                                                                                                 |                                            |
| Related                        | A clinical event, including laboratory test abnormality, where there is a “reasonable possibility” that the serious adverse event was caused by the study medication, meaning that there is evidence or arguments to suggest a causal relationship.             |                                            |
| Probably                       | A clinical event, including laboratory test abnormality, with a reasonable time sequence to drug administration, unlikely to be attributed to concurrent disease or other drugs or chemicals, and which follows a clinically reasonable response on withdrawal. |                                            |
| Possibly                       | A clinical event, including laboratory test abnormality, with a reasonable time sequence to drug administration, but which could also be explained by concurrent disease or other drugs or chemicals. Information on drug withdrawal may be lacking or unclear. |                                            |
| Unrelated                      | This category is applicable to adverse events which are judged to be clearly and incontrovertibly due to extraneous causes (diseases, environment, etc.) and do not meet the criteria for drug relationship listed for the above-mentioned conditions.          |                                            |

### 16.2.6 Serious Adverse Event

A Serious Adverse Event is any untoward medical occurrence (whether deemed to be related to investigational medication or not) that meets any of the following criteria:

- Fatal (i.e., the adverse event actually causes or leads to death)
- Life-threatening (i.e., the adverse event, in the view of the investigator, places the patient at immediate risk of death). This does not include any adverse event that, had it occurred in a more severe form or was allowed to continue, might have caused death.
- Requires or prolongs inpatient hospitalization
- Results in persistent or significant disability/incapacity (i.e., the adverse event results in substantial disruption of the patient's ability to conduct normal life functions)
- Congenital anomaly/birth defect in a neonate/infant born to a mother exposed to study drug
- Significant medical event in the investigator's judgment (e.g., may jeopardize the patient or may require medical/surgical intervention to prevent one of the outcomes listed above)

#### **16.2.7 Adverse Event Recording and Follow Up**

The investigator is responsible for evaluating and reporting any adverse events occurring during the study. The investigator will record onset, duration, intensity, any taken action, evolution/outcome, and the causality assessment for any adverse event.

Any adverse events leading to withdrawal from the study and those that persist at the end of the study must be followed up.

#### **16.2.8 Serious Adverse Events Reporting**

Although adverse events are recorded in the adverse event form of CRF special reporting requirements apply to the reporting of serious adverse events. Serious adverse events need to be reported immediately. The investigator should immediately notify the principal investigator of any serious adverse events that occurred at the trial site within 24 hours: MARVEL security desk [contact]

Serious adverse event reports will be collected centrally at the safety desk. Copies of all serious adverse event reports will be sent to the central trial management. Such preliminary reports will be followed by detailed descriptions, including anonymous copies of hospital case reports or related results, as well as other documents (if required and applicable). All serious adverse events that have not been resolved by the end of the study, or that have not been resolved upon discontinuation of the subject's participation in the study, must be followed until any of the following occurs:

- the event resolves
- the event stabilizes
- the event returns to baseline, if a baseline value is available
- the event can be attributed to agents other than the study drug or to factors unrelated to study conduct

- when it becomes unlikely that any additional information can be obtained

Any additional information known after the event has been initially reported should be sent using a new serious adverse event report form. New information will be noted on the "serious adverse event" form, by ticking the box marked "follow-up" and sending to MARVEL SAFETY DESK.

Patients who withdraw from the study treatment due to any adverse event will be followed up at least until the outcomes are determined, even if it implies that the follow-up continues after the patient has left the trial.

The investigator should assess the seriousness of the adverse events. This is based on the regulatory definitions of seriousness. The investigator should assess the causal relationship of serious adverse events. This is a clinical assessment of whether the adverse events may be related to the investigational medication. The evaluation of the expectedness is based on knowledge of adverse reactions and references.

